### Study protocol

1Baseline evaluation.1)All patients will undergo a history taking to determine whether they have previously received HPE therapy. The following tests will be performed to verify whether the patient had current HP infection prior to surgery: urea breath test, rapid urease test (RUT), and histological evaluation with Giemsa staining or immunohistochemistry (IHC).

HP infection will be diagnosed when any of the three studies showed positive results.All patients will be asked to take a 100 mg tablet of ^13^C-urea (UBiTkit; Otsuka Pharmaceutical Co., Ltd., Tokyo, Japan) with 100 mL of water after 4 h of fasting. Two breath samples will be collected before and 20 min after the patients swallow the tablet. A cut-off value of ^13^CO_2_ < 2.5% will be considered HP negative [15].

2)Gastric glandular atrophy and intestinal metaplasia, which are known precancerous conditions, will be evaluated in biopsy specimens obtained from the gastric antrum, body, and fundus by using the updated Sydney system. Serum pepsinogen I and II concentrations and pepsinogen I/II ratio will also be assessed.

Surgery. The patients will be subjected to curative gastrectomy with D1+ or D2 lymph node dissection based on clinical or surgical staging. Surgical treatment will be performed according to the gastric cancer treatment guidelines of Korea and Japan [16,17]. Reconstructive procedures will be selected depending on the surgeon’s preference.Patient enrollment. At the first outpatient clinic visit after surgery (3–4 weeks after surgery), consecutive patients with HP infection and pathologically proven stage 1 tumors will be enrolled in accordance with the following criteria for patient eligibility. Fig 2 presents a schematic diagram of the study protocol.The pathological stage will be determined on the basis of the results of the histopathological examination of the resected specimen. The depths of invasion (T stage) and lymph node involvement (N stage) of tumor cells will be evaluated according to the 8th edition of the International Union Against Cancer/American Joint Committee on Cancer Staging manual.Surgical curability is determined when pathological findings confirm the absence of residual tumor and an R0 resection has been achieved during the procedure.

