### Sample size calculation

On the basis of previous studies, we assumed that the 10-year incidence of adenoma and adenocarcinoma in the control group is approximately 10% [5,19]. The incidence of adenoma and adenocarcinoma will decrease by 50% after *H. pylori* eradication. According to this assumption, if the primary endpoint is exponentially distributed in both groups, the expected hazard ratio (HR) for the treatment group is 0.49. One interim analysis will be planned using the O’Brien-Fleming spending function at 50% of the total primary endpoint events. A total of 66 primary endpoint events will yield approximately 80% power to detect a HR of 0.49 with an overall type I error of 0.05 (two sided). Considering a 10% dropout rate, 984 randomized patients will be enrolled. The sample size will be calculated using PASS 15 software (NCSS, LLC, Kaysville, Utah, USA).

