### Statistical analysis

#### General considerations.

The full details of the statistical analyses will be described in the Statistical Analysis Plan (SAP), which will be finalised prior to code breaking. Analyses will be performed using SAS software (SAS Institute, Inc., Cary, North Carolina, USA); The version used will be specified in the SAP. Categorical data will be summarised by the number and percentage of subjects in each category. Continuous variables will be summarised by descriptive statistics, including the number of observations, mean, standard deviation, median, minimum, and maximum.

We will use the Kaplan-Meier method to calculate the cumulative incidence of adenoma, adenocarcinoma, and hyperplastic polyps, as well as overall survival. These will be compared between the two treatment groups using the log-rank test. The HRs, with 95% CIs, will be estimated using a Cox proportional hazards model. The improvement rate of precancerous lesion and the eradication rate of HP will be compared between treatment groups using the Chi-square test or Fisher’s exact test.

Unless otherwise stated, all efficacy analyses (except for the primary endpoint) will be conducted with a two-sided test at a significance level of α = 0.05.

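### The primary log-rank comparison, as written, uses neither the reconstruction strata nor the baseline mucosal markers; adding them is a small, low-cost improvement, not the correction of an error

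*Protocol article*

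**What the plan says.** Statistical analysis, General considerations, covers adenoma, adenocarcinoma, hyperplastic polyps and overall survival together. Cumulative incidence and survival are by Kaplan-Meier. On testing it says "These will be compared between the two treatment groups using the log-rank test", and on estimation "The HRs, with 95% CIs, will be estimated using a Cox proportional hazards model". No stratum or covariate is named for either. The same section says "The full details of the statistical analyses will be described in the Statistical Analysis Plan (SAP), which will be finalised prior to code breaking".

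The randomisation item (printed under Exclusion criteria) stratifies by reconstruction: distal gastrectomy with Billroth 1, Billroth 2 or Roux-en-Y, and proximal gastrectomy with double tract. The Discussion says this should control confounding and raise power, and cites differences in remnant cancer occurrence between reconstruction methods.

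Under Study protocol, Baseline evaluation, the article says "Gastric glandular atrophy and intestinal metaplasia, which are known precancerous conditions, will be evaluated in biopsy specimens" and "Serum pepsinogen I and II concentrations and pepsinogen I/II ratio will also be assessed". Atrophy and metaplasia return only as the reference for the secondary improvement endpoint. No analysis of pepsinogen is described.

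**The concern.** The protocol expects reconstruction to be prognostic and describes atrophy and metaplasia as precancerous. These are the factors one would want in the primary comparison, and the test as written uses none of them.

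- **Strata.** The power benefit that the Discussion expects comes in full only if the analysis carries the strata. If reconstruction is prognostic, an unstratified test after stratified randomisation tends to be conservative.
- **Baseline markers.** Randomisation does not balance them, so a chance imbalance passes straight into an unadjusted hazard ratio.

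At stake are a little power in a trial planned at about 80%, and small avoidable shifts in the estimate.

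**Working it through.** **1. The plan's own figures.** Inputs from Sample size calculation and Interim analysis: 10% control incidence at 10 years, halved to 5%; 66 events; 10% dropout; 984 randomised; final two-sided nominal alpha 0.049.

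- HR = ln(0.95)/ln(0.90) = 0.4868, stated as 0.49.
- Freedman events = (1.960 + 0.842)² × [(1 + 0.4868)/(1 − 0.4868)]² = 7.85 × 8.39 = 65.9, so 66. Schoenfeld gives 61.
- Power at 66 events (Freedman) is 80.1%, or 79.9% with the interim look.
- Mean incidence = (0.10 + 0.05)/2 = 0.075. N = 66/0.075 = 880, and 880/0.9 = 978, against 984 stated. Conversely, 984 × 0.9 × 0.075 = 66.4 events.
- O'Brien-Fleming nominal alphas are 0.00305 and 0.0490, matching Table 1.

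The stated design is reproduced, and its 80% is already the power of an unadjusted comparison.

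**2. Power gain from one baseline covariate.** Simulation with 886 evaluable patients (984 × 0.9), 10 years of follow-up, marginal incidence held at 10% and 5%, two-sided 0.049, and 4,000 trials per row. The Cox tests are Wald tests. Prognostic strength is an assumption, because the documents give none.

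| Covariate | Log-rank | Cox, unadjusted | Cox, adjusted | Gain over Cox | Gain over log-rank |
|---|---|---|---|---|---|
| No effect | 80.5% | 79.9% | 80.0% | 0.1 | −0.5 |
| HR 1.5 per SD | 80.3% | 79.7% | 80.2% | 0.5 | −0.1 |
| HR 2 per SD | 82.1% | 81.1% | 83.2% | 2.1 | 1.1 |
| HR 3 per SD | 82.3% | 81.7% | 86.3% | 4.6 | 4.0 |
| Binary (50%), HR 2 | 80.8% | 80.1% | 80.3% | 0.2 | −0.5 |
| Binary (50%), HR 3 | 80.9% | 80.2% | 81.0% | 0.8 | 0.1 |
| Binary (50%), HR 5 | 81.7% | 81.0% | 82.4% | 1.4 | 0.7 |
| Binary (50%), HR 10 | 80.4% | 79.7% | 81.6% | 1.9 | 1.2 |

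The Monte Carlo SE of each power is √(0.8 × 0.2/4000) = 0.6 points. A separate simulation (443 per arm, 2,500 trials per setting, unadjusted against adjusted Cox) agrees:

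- log HR 0.5 per SD: 80.4% to 80.9%
- log HR 0.8: 80.1% to 81.5%
- log HR 1.1: 80.1% to 84.6%
- log HR 1.4: 80.9% to 89.2%
- no prognostic value: 81.2% against 81.0%

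The last two prognostic settings correspond to HRs of exp(1.1) = 3.0 and exp(1.4) = 4.1 per SD.

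The gain does not come from tighter estimates. At HR 2 per SD the SD of the log HR was 0.266 unadjusted and 0.265 adjusted, while the median HR moved from 0.485 to 0.474. With about 7.5% of patients having an event, the adjusted HR lies slightly further from 1 and its spread hardly changes.

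**3. Chance imbalance.** With 492 per arm, the SE of a standardised mean difference is √(2/492) = 0.064. An imbalance of 0.1 SD is 0.1/0.064 = 1.6 SE, so one at least that large in either direction occurs in about 12% of trials. For log HR 0.8 per SD (assumed), the factor is exp(0.8 × 0.1) = 1.083, so 0.49 becomes 0.53 or 0.45. The SE of the log HR at 66 events is 2/√66 = 0.246, or √(1/22 + 1/44) = 0.261 with a 22/44 split. The shift is 0.08/0.25, about 0.3 SE.

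For a binary marker at 50% prevalence with HR 3, imbalances of 1 SD (3.2 percentage points) and 2 SD (6.4 points) move 0.49 to 0.506 and 0.522.

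**4. Not computed.** The gain from stratifying by reconstruction was not simulated, because the documents give neither stratum sizes nor stratum-specific risks.

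**The case against.** The strongest reply is that covariates in a Cox model are ordinary SAP content, and the article defers full details to a SAP that is not shown. This stands for the Cox model, which is never called unadjusted. It does not fully answer the point on the test: the article names a two-group log-rank comparison, and moving to a stratified, adjusted one changes the named method.

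Second, an unadjusted log-rank test is valid and conventional, and its error rate and confidence interval already allow for chance imbalance. That stands.

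Third, the markers may predict the remnant only weakly. Baseline scores "will be evaluated in biopsy specimens obtained from the gastric antrum, body, and fundus by using the updated Sydney system" before surgery, and some of that tissue is later removed. Pepsinogen taken then would reflect the whole stomach. This makes a very strong predictor harder to assume.

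Fourth, the change is not entirely free. Baseline work-up precedes surgery and enrolment follows 3–4 weeks after it, so complete data are not assured. There are only 33 events at the interim look and 66 at the end.

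A reader might infer that the trial is underpowered, or forgoes several points of power, without adjustment. The documents do not support that: the stated 80% is the unadjusted figure, and larger gains rest on a prognostic strength found nowhere in them. Nor does the absence of a stated pepsinogen analysis in a condensed article show that none is planned.

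**Conclusion.** The point holds as a minor improvement. The primary test as written leaves out both the randomisation strata, which the protocol itself expects to help, and baseline risk markers that it already plans to collect. The sample size and the validity of the test are unaffected.

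The expected gain from one covariate is about 0 to 2 points of power over an unadjusted Cox model. Against the planned log-rank test it is about −0.5 to 1.2 points in the same settings, and about 4 points only at HR 3 per SD. These figures assume a single perfectly measured covariate, proportional hazards, and no strata or interim look. The second benefit is removal of HR shifts of about 0.3 SE or less under the imbalances considered in the working. The strata are the better-supported half of the point, because the article's own Discussion relies on them.

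**What to change.** Before the 33-event interim look, settle the following in the protocol and SAP. The timing matters because SAP finalisation is tied only to code breaking, which the blinding text places at database lock.

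- Stratify both the log-rank test and the Cox model by the randomised reconstruction groups. Prespecify how sparse groups are combined.
- Adjust the Cox treatment term for at most one or two named baseline covariates, for example one updated Sydney atrophy/metaplasia grade from the body, with or without the log pepsinogen I/II ratio.
- If the covariates are meant to help power, state that the primary p-value comes from this treatment term, and name the form of the test. In the simulations the unadjusted Wald test ran 0.6 to 1.0 points below the log-rank test.
- Prespecify a rule for missing baseline values that keeps every randomised patient in the FAS.
- Keep the unadjusted log-rank test as a sensitivity analysis.

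The cost is a few lines of wording and code, with no extra patients or visits. The downsides are that the adjusted HR is conditional on baseline rather than marginal (at HR 2 per SD, 0.479 against 0.487 in the simulation set-up), and that 33 to 66 events leave room for few covariates and strata: with four reconstruction groups, 33/4 is about 8 events per group at the interim look.

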**Methods:**

After curative gastrectomy, patients with HP infection and pathologically proven stage 1 tumors will be enrolled and randomly assigned to eradication (n = 492) and placebo (n = 492) groups. Patients in the eradication arm will be given the eradication regimen, which will comprise 40 mg of esomeprazole, 1 g of amoxicillin, and 500 mg of clarithromycin twice a day for 14 days. The primary endpoint is the development of gastric neoplasms, including adenoma or adenocarcinoma. The secondary endpoints are the 10-year overall survival, improvement rates of gastric glandular atrophy and/or intestinal metaplasia, and incidence of new-onset hyperplastic polyps among the groups.

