#### Improvement rate of precancerous lesions.

Biopsy specimens will be obtained from three sites, namely, the fundus and greater curvature of the body in the remnant stomach and the anastomosis site, to assess gastric glandular atrophy and intestinal metaplasia. These parameters will be evaluated according to the updated Sydney system and compared with the scores assessed before surgery.

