#### Population analysis.

The details of each population below and any additional population, if needed, will be described in the SAP. The full analysis set (FAS) will be used as the primary population for all efficacy analyses. Dispositional summaries, demographic data, baseline characteristics, protocol deviations, and efficacy endpoints will be utilised for this analysis. In addition, the primary analysis will be repeated using the per-protocol (PP) set.

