#### FAS.

The FAS will include all randomized patients, which will constitute the intention-to-treat population. The FAS will be based on the treatment allocated (as randomized). All efficacy endpoints will be analysed using the FAS.

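### The improvement-rate endpoint has no stated denominator, and the blanket full-analysis-set rule would count patients with no baseline lesion, who cannot improve, in an unadjusted test

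*Protocol article*

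**What the plan says.** All references are to the protocol article.

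- **Endpoint.** The abstract's Methods paragraph lists improvement of glandular atrophy and/or intestinal metaplasia among the secondary endpoints: "The secondary endpoints are the 10-year overall survival, improvement rates of gastric glandular atrophy and/or intestinal metaplasia". The Objectives section repeats this.
- **Measurement.** Under Improvement rate of precancerous lesions, postoperative biopsies come from the fundus, the greater curvature of the body and the anastomosis. "These parameters will be evaluated according to the updated Sydney system and compared with the scores assessed before surgery". The article does not say what counts as improvement or who is in the denominator.
- **Baseline.** Under Study protocol, "Gastric glandular atrophy and intestinal metaplasia, which are known precancerous conditions, will be evaluated in biopsy specimens obtained from the gastric antrum, body, and fundus".
- **Test.** Under General considerations, "The improvement rate of precancerous lesion and the eradication rate of HP will be compared between treatment groups using the Chi-square test", with Fisher's exact test as the alternative. No baseline score or stratification factor is named.
- **Population.** Under FAS, "The FAS will include all randomized patients, which will constitute the intention-to-treat population", and "All efficacy endpoints will be analysed using the FAS".
- **Deferral.** Under Population analysis, "The details of each population below and any additional population, if needed, will be described in the SAP".
- **Eligibility.** Neither the inclusion nor the exclusion criteria mention atrophy or metaplasia.

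**The concern.** Improvement means a score lower than the one before surgery, and a patient who starts at 0 has nothing to lose. If such patients sit in the denominator, the reported rate mixes two things: how often lesions regress, and how many patients had one. An improvement rate of 14%, for example, could mean 35% of the patients with a lesion when 40% have one, or 14% of patients all of whom have one.

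The absolute difference between arms shrinks, and the test has less power than it would among patients who can respond. The named test also leaves out two variables that the trial already holds. One is the baseline score, which bounds how far a patient can improve. The other is the reconstruction method, by which randomisation is stratified. The Discussion says that this stratification is meant to improve power.

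At stake is the power and readability of one secondary endpoint. The primary endpoint is not involved.

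**Working it through.** **Is there a planned figure to reproduce?** No. The Sample size calculation section concerns only the primary endpoint. The article gives no rate, effect size or power for the improvement endpoint.

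**Inputs from the article.** 492 patients per arm (abstract); two-sided α = 0.05 for secondary efficacy analyses (General considerations).

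**Inputs assumed.** q is the share of patients with a baseline lesion. p_C and p_T are the improvement rates among those patients in the placebo and eradication arms.

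**Step 1: effect on the estimates.** With everyone in the denominator, the rates become q·p_C and q·p_T.
- Absolute difference: q·(p_T − p_C). Ten points become 8 at q = 0.8 and 5 at q = 0.5.
- Risk ratio: q·p_T / (q·p_C) = p_T / p_C, unchanged.
- If p_T = p_C the diluted rates are also equal, so type I error is preserved.

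**Step 2: effect on the test.** Let p̄ = (p_C + p_T)/2, d = p_T − p_C and n = 492. With pooled variance, the squared standardised difference is
- all randomised: n·q²d² / [2·q·p̄·(1 − q·p̄)] = n·q·d² / [2·p̄·(1 − q·p̄)];
- lesion at baseline only (n·q per arm): n·q·d² / [2·p̄·(1 − p̄)].

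The ratio of the first to the second is (1 − p̄)/(1 − q·p̄), which is below 1 whenever q < 1. Information is therefore lost. The loss is small when improvement is rare or q is near 1, and larger when improvement is common and many patients have no lesion.

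**Step 3: power.** With m patients per arm and rates a and b, whose mean is r:

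Power = Φ{ [√m·|b − a| − 1.96·√(2r(1 − r))] / √(a(1 − a) + b(1 − b)) }

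Worked example: 50% vs 60%, q = 0.5.
- All randomised: m = 492, rates 25% vs 30%. (22.18 × 0.05 − 1.96 × 0.6315)/0.6305 = −0.20, power 41.9%.
- Lesion only: m = 246, rates 50% vs 60%. (15.68 × 0.10 − 1.96 × 0.7036)/0.7000 = 0.27, power 60.7%.

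Power, all randomised → lesion at baseline only:

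| p_C vs p_T | q = 0.9 | q = 0.8 | q = 0.5 |
|---|---|---|---|
| 10% vs 18% | 92.7 → 93.1% | 89.1 → 90.0% | 69.2 → 72.6% |
| 20% vs 30% | 92.3 → 93.1% | 88.2 → 90.1% | 66.0 → 72.8% |
| 30% vs 40% | 86.1 → 87.8% | 79.9 → 83.8% | 54.1 → 64.3% |
| 50% vs 60% | 80.7 → 85.0% | 71.6 → 80.6% | 41.9 → 60.7% |

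**Step 4: a second set of assumptions.** Apply the planned 10% dropout (492 × 0.9 ≈ 443 assessable per arm) and assume 35% vs 50% among patients with a lesion. Power is 52% → 70% at q = 0.3, 66% → 82% at q = 0.4, 93% → 97% at q = 0.7 and 98.6% → 99.1% at q = 0.9.

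**Step 5: which sites can be paired.** Before surgery: antrum, body, fundus. After surgery: fundus, greater curvature of the body, anastomosis. Only body and fundus appear in both lists, and only where the operation leaves them. The anastomosis has no like-named baseline site.

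**The case against.** **The denominator is inferred.** The article never says that lesion-free patients count as non-improvers, and an improvement rate of a lesion can be read as a rate among those who have one. Full analysis details and further populations are left to a statistical analysis plan that is not shown. This stands in part. A reader might infer that the trial is committed to the diluted analysis, and the documents do not go that far. They do fix a rule for all efficacy endpoints and name an unadjusted test. An analysis plan that followed both literally would produce the dilution, and one that restricted the denominator would have to depart from the rule.

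**The size rests on assumptions.** This stands. A reader might take one scenario, such as 66% against 82%, as the expected loss. Nothing in the documents supports that prevalence or those rates, and the loss may be negligible.

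**The test is valid.** This also stands. Baseline lesion status precedes randomisation, type I error holds and the risk ratio is undiluted. It would be too much to say that the endpoint stops measuring improvement.

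**A proportional-odds model on follow-up scores would replace the stated endpoint.** Agreed. The adjustment should keep the binary improvement rate.

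**Conclusion.** The point holds in limited form. The article sets a blanket population rule and an unadjusted test for a rate whose denominator it does not define. Taken literally, that includes patients who cannot improve. The direction is certain: the absolute difference is multiplied by q, and power is lower whenever q < 1 and eradication has an effect. With 492 per arm and improvement of 10% to 50% on placebo, the assumed loss is 0.4 to 4 points at q = 0.9, 1 to 9 points at q = 0.8 and 3 to 19 points at q = 0.5. The documents cannot show where in that range the trial lies. This is a worthwhile correction to one secondary endpoint that has no stated power target. It is not a bias and does not touch the primary analysis.

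**What to change.** Before unblinding, state in the protocol or the statistical analysis plan:

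1. **Denominator.** Randomised patients, analysed as randomised, with a baseline score of at least 1 at a site sampled both before and after surgery (body and fundus, where these remain). Baseline status is fixed before randomisation, so the arms stay comparable. Word this as an explicit exception to the general full-analysis-set rule.
2. **Test.** A Cochran-Mantel-Haenszel test stratified by reconstruction method and baseline score, keeping improvement as a yes/no outcome.
3. **Anastomosis.** Report findings there separately, since no like-named baseline site exists.
4. **Patients with baseline 0.** Report new or worsening lesions separately.

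The cost is wording, slightly more analysis work and a denominator smaller than the full analysis set. No new data are needed, and sample size and the primary analysis do not change.
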